##### Analysis of secondary outcomes

Differences in the incidence of postoperative delirium and POCD will be presented as proportions and assessed with the use of a chi-square test. Odds ratios and 95% confidence intervals will be generated using logistic regression and interpreted. A parametric *t* test or non-parametric equivalent will be utilized to identify differences in POCD (MoCA scores) at each time point, controlling for baseline cognitive function. To account for the multiple measurements per subject, we will employ repeated measures regression techniques (e.g., analysis of variance). Although randomization should eliminate baseline confounders, univariate and multivariable logistic and linear regression modeling may be employed to assess the relationship between preoperative Lumosity use and both delirium and POCD, adjusting for any differences that may persist between groups.

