#### Statistical analysis

##### Sample size calculation

A convenience sample of 45 patients will be chosen to assess the feasibility of perioperative neurocognitive training. A total of 20 enrolled and randomized subjects are needed per group to assess the rates of participation, adherence, and dropout associated with the study. To account for patients who may fail the initial MOCA screen or withdraw, we have added five patients to the desired enrollment sample size for a total planned enrollment of 45 patients.

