##### Data analysis

Patients will be prospectively randomized using 1:1 block randomization. Analyses will be conducted using SAS version 9.4 (SAS Institute Inc., Cary, NC, USA) or later. Descriptive statistics of the data will be performed. Continuous data will be represented using mean (± standard deviation) or median (interquartile range) for variables not normally distributed and compared using parametric or non-parametric tests as appropriate. Categorical data will be presented as frequencies and proportions and compared using a chi-square or Fisher’s Exact test.

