In addition to these limitations, a potential source of bias in our study is the possibility for our assessors to become unblinded to group assignment throughout the course of a 6-month study period. We have taken many steps to prevent this occurrence and have systems in place to manage unblinding if it does occur. Throughout the course of the study, unblinded investigators will reiterate the importance of maintaining the blind, including detailed conversations both at the time of consent and prior to blinded study interactions (e.g., in-hospital cognitive assessments) on how to avoid potential conversations regarding the use of a mobile device in general. In an effort to maintain consistency, clearly defined roles have been delineated within the research group, with two unblinded team members solely responsible for monitoring adherence and technical support who are never involved in the assessment process. If an assessor does become unblinded, an alternate blinded team member trained in administering the CAM and MoCA is made available. If an alternate blinded team member is not available, the assessment is not performed and will be treated as missing data.

To summarize, elderly patients undergoing cardiac surgery have the highest incidence of postoperative delirium and POCD, which places them at an elevated risk for significantly higher perioperative morbidity and long-lasting detrimental effects on cognition. Neurocognitive training has been shown in preliminary studies to be effective in improving cognitive performance in the areas thought to be affected in the postoperative period. PEaPoD will be the first study to investigate the use of perioperative neurocognitive training in this high-risk patient population. Through the performance of this study, valuable information will be obtained that will guide future studies that are well designed to examine the technique’s efficacy in preventing postoperative delirium and POCD.

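### The per-visit t test or rank test on MoCA scores cannot control for baseline as stated; name one mixed model adjusted for the enrolment MoCA

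*Protocol article*

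**What the plan says.** Three sentences of the protocol article, under Analysis of secondary outcomes, bear on the MoCA scores.

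- Per visit, on the two-group comparison: "test or non-parametric equivalent will be utilized to identify differences in POCD (MoCA scores) at each time point, controlling for baseline cognitive function".
- Across visits: "we will employ repeated measures regression techniques (e.g., analysis of variance").
- Optionally: "univariate and multivariable logistic and linear regression modeling may be employed to assess the relationship between preoperative Lumosity use and both delirium and POCD", to adjust for differences that remain between the groups.

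The section on secondary outcomes (delirium and POCD) schedules a full MoCA at enrolment and five later assessments: a full MoCA on the day of surgery and at discharge, and a telephone MoCA at 1, 3 and 6 months. It says scores on the two instruments can be normalised. It also treats the day-of-surgery score as a renewed baseline.

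The Discussion says that an assessor who loses the blind is replaced by a trained, blinded alternate. Only if none is available, "the assessment is not performed and will be treated as missing data". The Discussion also says that the trial is not powered for clinical outcomes but should supply an effect size for powering larger studies.

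**The concern.** The first sentence pairs a method with an aim that the method cannot serve. A two-sample t test compares two means and a rank test compares two sets of ranks; neither has a place for a baseline score. The analyst would have to choose between ignoring baseline, using change scores and fitting a regression. These give different estimates and different precision, and the choice could be made after the data are seen.

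The second sentence does not settle the matter. It names a class of methods, and its only example, ANOVA, copes badly with missed visits in its classical form. The third does not either: it is optional, its exposure is preoperative training use rather than randomised arm, and it is not tied to each visit.

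With about 20 patients per arm there is little precision to spare, and the resulting estimate is meant to feed the design of a larger trial.

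**Working it through.** **The plan's own figure.** Sample size calculation: "A total of 20 enrolled and randomized subjects are needed per group", and "we have added five patients to the desired enrollment sample size for a total planned enrollment of 45 patients". 2 × 20 + 5 = 45, which reproduces and is not disputed. No power, alpha, standard deviation (SD), baseline correlation or missed-visit rate is given for the MoCA. The values of r and m below are therefore assumptions.

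**Step 1: precision at one visit.** Take equal SDs at baseline and follow-up, correlation r, and ignore the small cost of estimating the slope. Relative to a t test on raw scores (variance 1):

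- t test on change scores: 2(1 − r), because the baseline slope is fixed at 1
- ANCOVA: 1 − r²
- ANCOVA relative to change scores: (1 − r²) / [2(1 − r)] = (1 + r)/2

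| r | Change score | ANCOVA | ANCOVA / change score |
|---|---|---|---|
| 0.5 | 1.00 | 0.75 | 0.75 |
| 0.6 | 0.80 | 0.64 | 0.80 |
| 0.7 | 0.60 | 0.51 | 0.85 |

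In patients: to match ANCOVA on 40, a change-score test would need 40/0.85 = 47 to 40/0.75 = 53. At r = 0.3 the change score is worse than no adjustment at all (1.40 against 1.00), while ANCOVA still gains (0.91).

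**Step 2: patients left if classical ANOVA were used.** With a proportion m missed at each visit, independently, the expected complete cases are 40 × (1 − m)^k for k visits.

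| m | k = 5 (all post-enrolment) | k = 4 (postoperative only) |
|---|---|---|
| 5% | 31.0 | 32.6 |
| 10% | 23.6 | 26.2 |
| 15% | 17.7 | 20.9 |

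A likelihood-based model would use every observed score: at k = 5, about 190, 180 and 170 of 200, against 155, 118 and 89 for complete cases.

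**Step 3: both together.** A simulation of 1,000 trials used 20 per arm, five visits, equal correlations, an effect of 0.5 SD and data missing completely at random, with the covariance taken as known. At m = 10% the standard error of the average arm difference was:

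- r = 0.5: 0.19 SD for the baseline-adjusted model on all available scores, 0.32 SD for complete-case ANOVA without baseline
- r = 0.7: 0.17 SD against 0.37 SD

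The gap has two sources. At r = 0.5 the variance of a five-visit mean is (1 + 4 × 0.5)/5 = 0.60, so with complete data and no adjustment the standard error is √(2/20 × 0.60) = 0.245. Keeping 23.6 of 40 patients raises it to 0.245 × √(40/23.6) = 0.32. Baseline adjustment of complete data lowers it to √(2/20 × (0.60 − 0.25)) = 0.19.

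**The case against.** **The intention to adjust is stated, and a t test on change scores is an ordinary way to do it.** This is fair. On that reading the test is valid, and the gain from ANCOVA is one of precision. But the text names scores, not change, so the sentence still needs correcting. Comparison with an unadjusted t test overstates the gain, since the protocol does not intend to ignore baseline; the 75–85% ratio is the relevant one.

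**A reader might infer that the plan commits to repeated-measures ANOVA and so discards every patient with a missed visit.** The text does not support this. It says "repeated measures regression techniques (e.g., analysis of variance"), a class that already admits a mixed model. Loss of whole patients belongs to the classical form, not to likelihood-fitted versions. The choice of model and the handling of missing data may properly stand in an analysis plan that is not shown. What remains is that the single example is poorly suited to this schedule.

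**A reader might also infer that the trial discards an assessment whenever an assessor is unblinded.** It does not: the alternate assessor comes first.

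**The counts in Step 2 lean pessimistic.** Death, withdrawal and critical illness cluster within patients. If missingness were pure dropout reaching 15% by the last visit, 34 of 40 would be complete (40 × 0.85), not 18. The counts illustrate the risk and are not a forecast.

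**A mixed model is not a complete cure.** It assumes data missing at random, which is doubtful after critical illness, and it does not resolve death before a visit. An unstructured covariance for five visits has 5 × 6/2 = 15 parameters, many for about 40 patients. These points stand and set conditions on the fix.

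**Conclusion.** The point holds in a limited form. The per-visit sentence is wrong as written, because its tests cannot control for baseline, and nothing else in the section commits to an analysis that does. Under the nearest workable reading, ANCOVA has 75–85% of the variance of the planned test, given an assumed r of 0.5–0.7 and equal SDs. The ANOVA example is a lesser matter: a risk if taken in its classical form, of a size that depends on missed-visit rates the protocol does not give.

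The importance is modest. MoCA score is a secondary outcome, and feasibility is judged descriptively from recruitment and adherence, so it would be wrong to infer that the trial's main conclusion is in danger. The cost falls on the precision of the MoCA comparison and of the effect size carried into later trials.

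**What to change.** Replace the per-visit t tests with one likelihood-based mixed model for repeated measures:

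- **Patients:** all randomised patients with any post-enrolment score, using every available score.
- **Fixed effects:** arm, visit, arm-by-visit and the enrolment MoCA. Do not adjust for the day-of-surgery score: it is taken after training has begun, and adjusting for it could remove part of the training effect.
- **Scale:** put MoCA and telephone MoCA scores on one scale before modelling, and say how.
- **Covariance:** use a simple structure if about 40 patients do not support an unstructured one.
- **Report:** the adjusted arm difference with its 95% confidence interval at each visit.
- **Missing data:** state that scores are assumed missing at random, and report deaths separately by arm.

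The cost is a change of analysis wording. Sample size, visits and data collection stay as they are, and the model is standard in the SAS 9.4 software already named.

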## Methods and design

### Study design

The Prevention of Early Postoperative Decline (PEaPoD) study is a randomized, controlled, single-center, assessor-blinded clinical trial of eligible older adult cardiac surgical patients. Subjects will be randomized in a 1:1 allocation to either perioperative neurocognitive training or usual care control. The primary outcome of feasibility will be determined based on enrollment and protocol adherence. Secondary outcomes, including the incidence of postoperative delirium and POCD, will be evaluated using the Confusion Assessment Method (CAM) and the Montreal Cognitive Assessment (MoCA) respectively. Additionally, patients will be followed until 6 months postoperatively and evaluated via a telephonic MoCA (t-MoCA) to assess the presence of long-term POCD and to map the trajectory of return to baseline cognitive function. A study schema is provided in Fig. 1. Our study protocol was written according to the principles outlined in the Standard Protocol Items: Recommendations for Interventional Trials (SPIRIT) checklist (Fig. 2, Additional file 1) [20].

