#### Study outcomes

##### Primary outcome: feasibility

To best evaluate the potential effect of a neurocognitive training program on the development of postoperative delirium and POCD, a large randomized controlled trial would need to be performed. However, before undertaking such a trial, it is imperative to show that implementation of a prehabilitative program is feasible. This is especially true given the heavy reliance on a patient-performed intervention and need for recruitment of interested subjects with sufficient lead-in time for the intervention to be effective. Furthermore, since this is the first time neurocognitive training will be implemented in this setting, there is no preliminary data regarding a potential effect size for an accurate power calculation to be performed. Therefore, the PEaPoD trial was designed to evaluate feasibility as a primary outcome. Feasibility will be assessed through both recruitment and adherence. Satisfactory recruitment will be defined as enrollment of 50% or more of eligible patients, which will reflect efficient screening and approach procedures and also sufficient interest within this patient population. Adherence will be quantified for analysis using automated gameplay data recorded during use. Consideration of three separate training periods (preoperative, immediate postoperative, and extended postoperative periods) will be taken into account in evaluating optimal adherence patterns for potential future study.

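### The optional secondary regression takes preoperative training use as its exposure and picks covariates from observed imbalance; it should use randomised group and a fixed baseline covariate

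*Protocol article*

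**What the plan says.** The section Analysis of secondary outcomes in the protocol article first sets out what will be done. Delirium and POCD are compared between groups as proportions, "assessed with the use of a chi-square test", with odds ratios and 95% confidence intervals from logistic regression. MoCA scores are compared with control for baseline cognition and with repeated-measures methods.

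A last sentence then adds an option. It opens "Although randomization should eliminate baseline confounders" and allows univariate and multivariable logistic and linear models "to assess the relationship between preoperative Lumosity use and both delirium and POCD, adjusting for any differences that may persist between groups". The section does not say whether use means the assigned arm or the time played. Its only covariate rule is that differences between the groups are adjusted for.

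Four other places bear on this:

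- Study intervention: neurocognitive training expects playing time to differ between patients because of scheduling.
- Analysis of the primary outcome measures adherence in minutes and reports the preoperative period separately.
- Control arm: usual care asks controls not to open an account.
- Discussion hopes that the trial's effect estimate will help power larger studies.

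**The concern.** Three things look wrong in that sentence.

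1. **Exposure.** Randomisation protects a comparison of assigned groups. It does not protect a comparison of patients who trained more with patients who trained less. Training time is decided after randomisation, partly by how long the patient waits for surgery. If waiting time, or anything else that drives playing time, also relates to delirium or cognition, the coefficient for use mixes that relation with any effect of training.

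2. **Covariates.** Adjusting for whatever differs between the arms lets chance choose the model. An imbalance says nothing about whether a variable predicts the outcome, and a strong predictor that happens to be balanced would be left out. The adjusted answer stays open until the data are seen.

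3. **Events.** About 40 patients give few events for a multivariable logistic model, and the rule sets no limit on covariates.

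At stake is the effect estimate. The article says of the intervention that "there is no preliminary data regarding a potential effect size for an accurate power calculation to be performed", so this trial's estimate is what a later trial would start from. An exaggerated estimate would make that trial too small.

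**Working it through.** **Inputs**

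- Randomised patients: 40. Sample size calculation says "A total of 20 enrolled and randomized subjects are needed per group", and "we have added five patients to the desired enrollment sample size for a total planned enrollment of 45 patients". Check: 2 × 20 + 5 = 45, which reproduces the stated enrolment.
- POCD rate: about 30% at 6 months (Background).
- Delirium rate: the article gives no percentage. I assume 15% to 50%.
- The article gives no significance level, power or effect size for these outcomes, so there is no power figure to reproduce.

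**Which reading of use?** For minutes played: the sentence says preoperative, whereas the arm's programme continues for 4 weeks after surgery; preoperative minutes are a quantity the trial will report; and group odds ratios have already been provided for. For assigned arm: the sentence begins with what randomisation achieves and ends with differences between groups, and controls should have no use at all. The text does not settle it.

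**Expected events** = patients × rate.

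- POCD: 40 × 0.30 = 12.
- Delirium: 40 × 0.15 = 6 to 40 × 0.50 = 20 (assumed range).

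**Events per coefficient** = events / (1 exposure + number of covariates).

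| Model | POCD, 12 events | Delirium, 6 to 20 events |
|---|---|---|
| Exposure only | 12/1 = 12 | 6 to 20 |
| + 1 covariate | 12/2 = 6 | 3 to 10 |
| + 2 covariates | 12/3 = 4 | 2 to 6.7 |
| + 3 covariates | 12/4 = 3 | 1.5 to 5 |
| + 5 covariates | 12/6 = 2 | 1 to 3.3 |

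The common guide of 10 events per coefficient is a rule of thumb and not from the article. By it, 12 events carry the exposure alone.

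**How often the covariate rule is triggered by chance.** The article does not say how a difference is judged. If it were p < 0.05 on independent baseline variables, the chance of at least one is 1 − 0.95^m:

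- 5 variables: 1 − 0.95^5 = 23%
- 10 variables: 1 − 0.95^10 = 40%
- 20 variables: 1 − 0.95^20 = 64%

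**What surplus covariates do to the logistic estimate.** I simulated 20 per arm by assigned group, with 2,000 runs per setting, an assumed control rate of 30%, an assumed true odds ratio of 0.40 and covariates of pure noise. The treated rate is then (0.4286 × 0.40)/(1 + 0.4286 × 0.40) = 14.6%, so about 20 × 0.30 + 20 × 0.146 = 8.9 events.

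| Noise covariates | Mean log OR / true log OR | SD of log OR |
|---|---|---|
| 0 | 1.06 | 0.84 |
| 3 | 1.16 | 1.05 |
| 5 | 1.28 | 1.28 |

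About 4 to 5% of fits could not be estimated and were left out. The drift away from no effect and the loss of precision come from the extra terms alone. The sizes depend on the assumed rate and odds ratio.

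**The case against.** The strongest reply is that this is an optional extra in a declared feasibility trial. The analyses the article commits to compare the groups as randomised, and nothing in the optional sentence replaces them. That is right. A reader might infer that the secondary analysis as a whole abandons randomisation; the text does not support this. Nor does adjusting for baseline variables in itself break randomisation. Only an exposure defined by actual use would do so.

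The second reply is that preoperative use is simply a loose name for the training arm. This is a fair reading and cannot be excluded. It would remove the exposure problem but leave the covariate rule as it is.

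A reader might also go further and expect a spurious protective effect of a particular size, on the ground that fitter patients train more. The article says only that scheduling will make playing time unequal. It says nothing about fitness, so any odds ratio computed for such a mechanism reflects the inputs chosen for it. The direction and size of a bias are unknown.

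The chi-square test might seem to lack a small-sample alternative. It does not: Data analysis says that categorical data are "compared using a chi-square or Fisher’s Exact test". At the article's 30% rate the expected number of events per arm is 12/2 = 6, above the usual threshold of 5.

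Finally, covariate lists are commonly left to an analysis plan that is not shown here. That answers a missing list, but not a stated rule of choosing from observed differences. The few-events argument is also limited: it concerns the logistic models, not the linear models of MoCA scores in the same sentence.

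**Conclusion.** The point holds in a limited form. The exposure is badly worded: read as minutes played, it yields a non-randomised estimate that may be biased by an unknown amount; read as assigned arm, it yields no such bias. Under both readings the covariate rule is data-driven and has no cap, and about 12 POCD events cannot carry several covariates in an ordinary logistic model: three leave 3 events per coefficient, five leave 2. For delirium the range is wider, because its rate is assumed.

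The committed group comparison is untouched, and the outcomes are secondary in a trial that says it is not powered for them. The consequence is therefore modest. It deserves correction because the article intends the effect estimate to inform the size of later trials, and because the correction is cheap.

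**What to change.** Replace the last sentence of Analysis of secondary outcomes with wording to this effect:

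- In every model for delirium and POCD the exposure is the randomised group.
- Models adjust for the MoCA score at enrolment, whatever the observed balance. Age may be added as a second fixed covariate, and no others. The score should be the enrolment one, because the MoCA on the day of surgery is taken after training has begun.
- Binary outcomes are fitted by Firth or exact logistic regression.
- Any analysis of minutes played is labelled exploratory and non-randomised.

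The event count limits this proposal too. Group plus enrolment MoCA gives 12/2 = 6 events per coefficient, and adding age gives 12/3 = 4. Hence the penalised or exact method, and the preference for one covariate.

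Enrolment MoCA, age and minutes are already collected, so the change is to the analysis text only. The price is less freedom to add covariates later.
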